## Abstract

**Background:**

The identification of factors associated with functional impairment, in particular those which are potentially modifiable, may help to delay the advanced stages of functional dependence in patients with neurocognitive disorders such as Alzheimer’s disease and related disorders.

The objectives of the MEMORA cohort are to investigate the factors associated, first with functional autonomy change over time, and secondarily with the cognitive performance and behavioral disorders changes over time.

**Methods:**

The MEMORA study is a multicenter prospective cohort study carried out throughout the patient’s care pathway, in Memory centers of Lyon (France). The study will include 6780 patients at all stages of memory disorders in 6 years. The follow-up for each patient is planned for 3 years. The main outcome is the functional autonomy level change as assessed by the instrumental abilities of daily living (IADL) score. Patient characteristics include sociodemographic and clinical features, neuropsychological performance, pharmaceutical and non-pharmaceutical therapy.

**Discussion:**

This study conducted in a context of routine care may help to identify the factors associated with functional impairment related to progressive neurocognitive disorders. Subsequently, interventions on potentially modifiable factors could be proposed to the patients to improve their management and delay functional dependence.

**Trial registration:**

NCT02302482, registered 27 November 2014.

## Background

Alzheimer’s disease and related disorders (ADRD) result in cognitive loss that progress towards functional loss of autonomy, and behavioral disorders [1, 2]. The decline of functional abilities and cognitive performance, as well as a behavioral disturbance are among the main predictors of nursing home placement, and therefore represent an important burden for the family and the society, and a public health stake [3]. Previous studies have identified a number of potential risk factors for ADRD, major neurocognitive disorders (NCD), or cognitive decline i.e. high blood pressure, vascular risk factors, stroke, arterial fibrillation, diabetes mellitus, hypercholesterolemia, hyperhomocysteinemia, biological inflammation, genetic biomarkers, obesity, sedentary lifestyle, smoking habit, depression, educational level [1, 4–6]. Nevertheless, the role of some of these factors on the progression of the NCD remains unclear [7, 8]. In addition, there is little published data on to the risk factors for loss of functional autonomy in patients at all stages of NCD. Indeed, the previous published studies have considered either community-dwelling elderly subjects without NCD at inclusion, or patients with AD among whose functional autonomy was already altered [9–12].

As research for a curative treatment of ADRD continues, identifying and improving the understanding of the factors implicated in the progression of functional disability could allow to develop and propose interventions to target potentially modifiable factors with the perspective to prevent or slow the functional disability in patients with NCD [13, 14].

The MEMORA cohort, including patients followed in memory centers (MC), has been designed to study the determinants for functional decline of patients at all stage of memory troubles including subjective cognitive decline (SCD), and minor or major neurocognitive disorders (NCD) [15, 16].

In this manuscript, the MEMORA study protocol is presented.

## Methods

### Aims

#### Primary aim

The primary aim of the MEMORA cohort is to study the relationship between patient characteristics and functional autonomy change over time among patients attending a MC, including neuropsychological performance, pharmaceutical and non-pharmaceutical therapy, clinical and sociodemographic characteristics.

#### Secondary aims

The secondary aims are to investigate the factors associated with cognitive performance and its change over time, and those associated with behavioral disorders.

### The MEMORA cohort design

The MEMORA cohort is a prospective, open study, started in November 2014 and conducted in a context of routine care (Table 1). The study includes patients over a period of 6 years, and each patient is followed for 3 years. The data collection is carried out throughout the care pathway. At the first visit, patients undergo a clinical examination with a medical specialist (neurologist, geriatrician, or psychiatrist). Evaluations are performed at baseline and include functional autonomy level, cognitive performance and presence and severity of behavioral disorders; depending on their cognitive status patients may be referred to a neuropsychological examination. Patients are then routinely followed-up and data are prospectively collected in an electronic Case Report Form (eCRF) using the Easily® software (University Hospital of Lyon, France); the interval between visits is 6 months to 1 year as planned in routine care by the physician in charge of the patient. The number of follow-up visits per patients has not been determined in advance and may vary from a patient to another.

**Table 1 Tab1:** Flow diagram of the MEMORA-cohort

Timepoint	*Study periods*		
	*Enrollment*	*Initial assessment*	*Follow-up*
	- *t1*	0	*ti:delay to 6 months to 1 year*
Enrolment:			
Eligibility screen	X		
Information to patients/careviger	X		
Collection of non-opposition to participate	X		
Date of the visit	X	X	X
Assessments:			
*Primary outcome:*			
Functional autonomy level (IADL, DAD-6)		X	X
*Secondary outcomes:*			
Global cognitive performance (MMSE)		X	X
Behavioral disorders (NPI)		X	X
*Characteristics*:			
Sociodemographic data (age, gender, educational level, socio professional categories, marital status, geographical location)		X	
Relationship with the primary caregiver		X	
Current lifestyle		X	
Patient protection measure		X	
Neuropsychological evaluation		X	X
Diagnosis and stage		X	X
Comorbidities, lifestyle habits		X	
Pharmaceutical therapeutics		X	X
Non-pharmaceutical therapeutics		X	X
Caregiver burden (Mini-Zarit)		X	X

### Study sites and population

The MEMORA cohort includes patients attending the MC of the Charpennes Hospital, Villeurbanne, France since 2014, and has been extended since 2017 to the MC of the Dugougon Hospital, Lyon, France. The MC role is to offer evaluation and follow-up for patients with cognitive disorders, generally referred by a general practitioner or medical specialists.

Inclusion criteria are: attending a medical appointment in the MC, living at home or in retirement facility. The patients are informed of the study and its objectives and are given the opportunity to object to participation. Exclusion criteria are: hearing or visual impairment preventing cognitive assessment, institutionalization, being under legal protection.

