### Primary outcome

The primary outcome of the MEMORA cohort is the change in the level of functional autonomy that is assessed using the 8-item version of the Lawton Instrumental Activities of Daily Living (IADL) score, and the 6-item version of the Disability Assessment for Dementia scale (DAD-6) [17, 18]. In the MEMORA study, the functional scales are collected during an interview of the primary caregiver or the patient with a physician, a nurse, or a psychologist. The change in functional autonomy will be measured using successive scores measured during patient follow-up visits at the MC.

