#### Sample size

This study is designed to be descriptive rather than analytical. Based on the number of patients attending a memory consultation in the MCs and meeting the inclusion criteria, the number of patients that can be included in the study has been estimated at 1130 per year. As the means available allow to plan an inclusion for 6 years, the sample size is estimated at 6780 patients. With an expected loss of follow-up of 20% in the context of patients with cognitive disorders, the corrected sample size reaches 5650 patients. In case an association between one factor of 2 categories and the outcome change over time is to be assessed, this sample size would allow to detect an effect size of 0.1 between the 2 patients categories, at a risk alpha of 0.05, with a power of 96%. In case of factor with more than 2 categories, the power would reach 99%. This number of subjects seems sufficient to allow to assess the associations between various factors and the outcomes of the primary and secondary objectives.

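### Entry is not limited to a first memory-centre consultation and no date of first consultation or diagnosis is listed, so survivor selection may bias associations with functional change by an amount that the listed data cannot show

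*Protocol article*

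**What the plan says.** All references are to the Protocol article.

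- **Study sites and population**, on entry: "Inclusion criteria are: attending a medical appointment in the MC, living at home or in retirement facility". On exclusions: "Exclusion criteria are: hearing or visual impairment preventing cognitive assessment, institutionalization, being under legal protection". On the centres: "The MC role is to offer evaluation and follow-up for patients with cognitive disorders".
- **Abstract, Methods**: "The study will include 6780 patients at all stages of memory disorders in 6 years".
- **The MEMORA cohort design**: "At the first visit, patients undergo a clinical examination with a medical specialist". Whether this visit is the first at the centre or the first in the study is not said.
- **Sample size**: the 1130 inclusions per year are estimated as "Based on the number of patients attending a memory consultation in the MCs and meeting the inclusion criteria", with no mention of new referrals.
- **Table 1** puts time 0 at the initial assessment. It lists diagnosis and stage, comorbidities and therapies, but no date of first MC consultation, date of diagnosis or disease duration.
- **Primary outcome**: "The change in functional autonomy will be measured using successive scores measured during patient follow-up visits at the MC". **Primary analysis** models these scores in a generalized linear mixed model, adjusts for confounders where appropriate, and names no time scale.

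**The concern.** Under the criterion as worded, a patient who had attended for years when the study opened at a centre (2014 or 2017) qualifies on the same terms as a new referral. Such a patient can enter only if decline has not yet led to an institution or to legal protection. The Background section itself names functional decline among the main predictors of nursing home placement, so this filter acts on the primary outcome. Patients who declined fast before enrolment are under-represented, and more so among carriers of a factor that speeds decline.

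The primary aim is the relation of patient characteristics, including therapies, to change in autonomy, with interventions on modifiable factors as the later goal. A factor's association with decline could be distorted. Therapies already under way at entry are particularly exposed, because their users are those who remained eligible. With neither date in the listed data, the distortion could not be examined.

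**Working it through.** **1. Who can enter.** The criterion requires an appointment, not a first one. The centres offer follow-up as well as evaluation, all stages are admitted, and the recruitment figure counts attenders: 6 × 1130 = 6780, which matches the stated total. Nothing shown closes entry to patients already in follow-up.

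**2. What would separate the two groups.** Stage and score at entry are recorded, but both are results of earlier decline. Neither date that would mark a patient as new or already followed is in Table 1.

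**3. Possible size, linear decline.** The documents give no figure on this point, so every input here is an assumption. The IADL level at t years after first consultation is y0 + s·t, with:
- y0 ~ N(6, 1.5²);
- s = min(0, −(0.30 + 0.15x) + e), where x is a binary factor carried by half the patients and e ~ N(0, σ²) with σ = 0.3 or 0.5;
- a patient enrolled at lag L is kept only if y0 + s·L > 3.

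Simulated slope difference between carriers and non-carriers (points/year), by lag at enrolment:

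| σ | lag 0 | 3 years | 5 years | lags uniform over 0–5 |
|---|---|---|---|---|
| 0.3 | 0.1340 | 0.1186 | 0.0928 | 0.1225 |
| 0.5 | 0.1160 | 0.0834 | 0.0525 | 0.0951 |

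Repeat runs differ by up to about 0.003. The loss is 11–28% in patients enrolled at 3 years and 31–55% at 5 years, but those are subgroups. For a pooled sample with already-followed share p, the weighted difference is (1 − p)·D(new) + p·D(followed):
- σ = 0.3, p = 0.25: 0.75 × 0.1340 + 0.25 × 0.1225 = 0.1311, which is 2% lower.
- σ = 0.3, p = 0.50: 0.1283, which is 4% lower.
- σ = 0.5, p = 0.25: 0.75 × 0.1160 + 0.25 × 0.0951 = 0.1108, which is about 5% lower.
- σ = 0.5, p = 0.50: 0.1056, which is 9% lower.

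The pooled loss is therefore about 2–9%. A larger share or longer lags raise it.

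**4. Dependence on the exit rule.** If only half of those at or below 3 leave, the already-followed figures are 0.1291 and 0.1075. Pooled at 50%, these give (0.1340 + 0.1291)/2 = 0.1316 (2% lower) and (0.1160 + 0.1075)/2 = 0.1118 (4% lower).

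**5. Direction.** A second model uses y0 ~ N(6.5, 1), slope −0.5 − 0.3x + N(0, 0.35²) and a lag uniform over 0.5–8 years. Patients are kept if they are above a threshold of mean 2.5 (SD 0.5), and change is taken over the next 3 years.
- *Linear decline:* −0.300 in new patients and −0.261 in already-followed ones (13% smaller). Pooled at 25/50/75% the result is −0.294/−0.287/−0.273 (2–9% smaller).
- *Less slope variation:* with slope SD 0.10 the already-followed value is −0.295; with SD near 0 it is −0.300, so there is no bias.
- *Accelerating decline* (adding 0.1·s·t²): −0.390 in new patients, −0.456 in already-followed ones, and −0.416 pooled at 50%. The pooled value is 0.416/0.390 = 1.07 times the new-patient one. Selection still acts here, since without it the already-followed value would be −0.647. It is outweighed because these patients are observed later on a steepening course.

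**The case against.** The strongest reply is that entry may in practice be at first contact. The cohort design section describes a specialist examination at the first visit, possible neuropsychological referral, then routine follow-up, and patients are generally referred by a general practitioner or specialist. That order fits a new-referral work-up. This stands as a plausible reading, but the phrase is undefined and the eligibility criterion does not carry it. A reader might infer that long-followed patients are in fact pooled. The documents establish only that the criterion permits it, and they give no share.

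A reader might also infer that the model counts time from inclusion. Table 1 puts 0 at the initial assessment, but that is a schedule, and the model's time scale may properly sit in an analysis plan. That part is no finding.

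It can also be said that the groups are separable, because medical records are a data source and medical history is collected. That stands in part: the dates can probably be retrieved, which is why the remedy is cheap, but neither is among the listed variables.

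Adjusting for baseline stage or score does not answer the point. In the first model with σ = 0.3, adjustment for entry score lowers the slope difference further, from 0.118 to 0.101 at 3 years and from 0.092 to 0.071 at 5 years.

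Finally, the study calls itself descriptive, seeks patients at all stages, and says that known biases will be considered in interpretation. This weighs against replacing the main population. It does not weigh against collecting a date, without which this bias cannot be assessed.

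**Conclusion.** The point holds as a gap in the entry definition and the listed data. Entry is open at any MC appointment, the exclusions remove patients who have already progressed to an institution or legal protection, and nothing listed distinguishes new from already-followed patients. Survivor selection may therefore bias associations with change, often toward the null.

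A reader might infer that harmful factors will be underestimated. The documents do not support that certainty: the bias vanishes when slopes hardly vary, and under accelerating decline the pooled estimate exceeds the one in new referrals. Nor should the 11–55% losses be read as the effect on the study, since they describe patients enrolled only 3 or 5 years after first consultation. The pooled figure is about 2–9% at a 25–50% already-followed share. It rests on an assumed starting score, slope SD, lag range and exit at IADL 3 or below, none of which is in the documents. No figure was worked out for therapies already under way; for them the argument is qualitative.

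This is a modest but inexpensive improvement, not a flaw that undermines the cohort.

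**What to change.** 1. State whether the first visit in the cohort design section is the first MC consultation. If entry is limited to it, say so in the inclusion criterion, and the point is closed.
2. If it is not, take the date of first MC consultation, and of first diagnosis where recorded, from existing records into the eCRF for all patients, including those already enrolled.
3. Keep the all-stages cohort as the main population. Making first-consultation patients primary would work against the stated aim.
4. Include time since first consultation in the mixed model, with its interaction with follow-up time. This lets slopes differ by prior follow-up, but does not by itself undo selection among already-followed patients.
5. For that reason, pre-specify a sensitivity analysis in patients included at their first consultation, reported beside the main result, especially for therapies already under way at entry.

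The cost is limited extra data extraction and a smaller sample, hence less precision, in the sensitivity analysis.

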#### Ethical and legal considerations

Information is individually provided to the patients and caregivers at inclusion. The MEMORA cohort protocol (clinicaltrial.gov number NCT02302482) has been approved by the regional ethics committee (*Comité de protection des personnes Sud Est III*) on July 29, 2014. Data processing has been approved by the national data protection commission.

### Primary outcome

The primary outcome of the MEMORA cohort is the change in the level of functional autonomy that is assessed using the 8-item version of the Lawton Instrumental Activities of Daily Living (IADL) score, and the 6-item version of the Disability Assessment for Dementia scale (DAD-6) [17, 18]. In the MEMORA study, the functional scales are collected during an interview of the primary caregiver or the patient with a physician, a nurse, or a psychologist. The change in functional autonomy will be measured using successive scores measured during patient follow-up visits at the MC.

### Secondary outcomes

The secondary outcomes include global cognitive function measured using the Mini-Mental State examination (MMSE) [19], and behavioral disorders measured using the Neuropsychiatric Inventory (NPI) [20]. The MMSE score ranges from 0 to 30 (optimal cognitive performance) and is collected during an interview with the patient by a physician, a nurse, or a psychologist. The NPI score ranges from 0 to 144 (a higher score indicating a greater number/severity of disorders) and is collected during an interview with the primary caregivers by a physician, a nurse, or a psychologist.

### Patient characteristics and evaluations

The patient characteristics and evaluations collected in the MEMORA study are listed in Table 1. Diagnosis stage and etiologies are determined by the medical specialist in charge of the patient (neurologist, geriatrician, or psychiatrist). Patients with a subjective cognitive complaint and absence of objective evidence (i.e. normal neuropsychological performance), are considered having SCD [16]. Mild and major neurocognitive disorders (NCD) are identified using the Diagnosis and Statistical Manual of mental disorders (DSM-V) nomenclature [15]. Previous medical history, family history of dementia, and comorbidities are also collected. The neuropsychological tests are chosen in a set of 142 tests allowing examining different cognitive functions (memory, executive functions, and instrumental abilities) by the psychologist, based on the patient’s cognitive status and the patient’s complaint or his entourage. The pharmacological drugs used by the patient are collected from the current general practitioner prescription and the specialist prescription at the MC. Home services, such as nurse care, day care admission, speech therapy, physical therapy, psychological support, cognitive rehabilitation or other non-pharmacological treatments are also collected. The caregiver burden is evaluated for the main caregiver who accompanies the patient at the MC using the mini-Zarit questionnaire [21].

#### Sample size

This study is designed to be descriptive rather than analytical. Based on the number of patients attending a memory consultation in the MCs and meeting the inclusion criteria, the number of patients that can be included in the study has been estimated at 1130 per year. As the means available allow to plan an inclusion for 6 years, the sample size is estimated at 6780 patients. With an expected loss of follow-up of 20% in the context of patients with cognitive disorders, the corrected sample size reaches 5650 patients. In case an association between one factor of 2 categories and the outcome change over time is to be assessed, this sample size would allow to detect an effect size of 0.1 between the 2 patients categories, at a risk alpha of 0.05, with a power of 96%. In case of factor with more than 2 categories, the power would reach 99%. This number of subjects seems sufficient to allow to assess the associations between various factors and the outcomes of the primary and secondary objectives.

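### A 20% loss from 6780 patients leaves 5424, not the 5650 stated as the corrected sample size; the printed 96% power survives the correction

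*Protocol article*

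**What the plan says.** The whole calculation stands in the Sample size section of the protocol article. It starts from feasibility: "the number of patients that can be included in the study has been estimated at 1130 per year". It continues: "As the means available allow to plan an inclusion for 6 years, the sample size is estimated at 6780 patients". It then allows for attrition: "With an expected loss of follow-up of 20% in the context of patients with cognitive disorders, the corrected sample size reaches 5650 patients".

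The power statement follows directly: "this sample size would allow to detect an effect size of 0.1 between the 2 patients categories", at alpha 0.05 and with a power of 96%. For factors with more than two categories the section gives 99%. The Primary analysis section adds that tests are two-sided. The Sample size section also describes the study as descriptive rather than analytical.

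**The concern.** The section prints an enrolled number, a loss rate and a retained number. Any two of these fix the third, and the three printed values are not consistent. The retained number is also the one that the power sentence goes on to use, so the error sits in a planning figure on which a later statement rests.

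Two things are at stake. One is whether the stated power still holds on the number that the plan's own loss rate delivers. The other is the benchmark for retention. The Descriptive analyses section plans a flow-chart of patients with follow-up visits and a comparison of patients with and without complete follow-up. A reader who sets observed retention against the plan would find 20% loss stated and 16.7% loss implied.

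**Working it through.** **Inputs**, from the Sample size section unless noted:

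- Inclusions per year: 1130, for 6 years
- Expected loss to follow-up: 20%
- Corrected sample size as printed: 5650
- Effect size: 0.1, read here as a standardised mean difference (an assumption, since the article does not name the metric)
- Alpha: 0.05, two-sided (Primary analysis section)
- Equal group sizes (an assumption, since no category split is given)

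**Enrolled number.** 1130 × 6 = 6780. This reproduces the printed figure.

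**Retained number.** Retained = enrolled × (1 − loss) = 6780 × 0.80 = 5424. This does not reproduce 5650.

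- Difference: 5650 − 5424 = 226 patients, and 226 / 5424 = 4.2%.
- Loss implied by the printed number: 1 − 5650 / 6780 = 16.7%.
- Exact match: 6780 / 1.2 = 5650.

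**Reading it in reverse.** Suppose 5650 were the target and 6780 the inflated enrolment. The correct inflation would be 5650 / 0.80 = 7062.5, rounded up to 7063, not 6780. The section also derives 6780 from yearly attendance, not from a target. So this reading does not reconcile the figures either.

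**Power, two equal groups.** With N patients in total and a normal approximation, power = Φ(d × √(N/4) − 1.96).

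- N = 5650: 0.1 × √1412.5 = 3.758; 3.758 − 1.960 = 1.798; power = 96.4%. The printed 96% is reproduced.
- N = 5424: 0.1 × √1356 = 3.682; 3.682 − 1.960 = 1.722; power = 95.7%.
- N = 6780, for comparison: 98.4%. The printed 96% therefore matches the corrected number and not the enrolled one.

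A two-sample t-test calculation gives the same values (0.9639, 0.9574 and 0.9845). A power of exactly 96% would need 5508 patients in total. So 5424 falls just short of 96.0%, but still rounds to 96%.

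**Sensitivity to unequal groups** (the splits are illustrative and do not come from the article):

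| Split | N = 5650 | N = 5424 |
|---|---|---|
| 1:1 | 96.4% | 95.7% |
| 2:1 | 94.3% | 93.5% |
| 4:1 | 85.2% | 83.8% |

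The change due to the attrition figure stays below 1.5 percentage points in each row. The much larger fall down the columns comes from the imbalance.

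**The 99% for more than two categories.** If 0.1 is read as Cohen's f, power exceeds 99.9% at both sample sizes for 3 to 10 equal groups. If f = 0.05, the two-group equivalent of a standardised difference of 0.1, power for three groups is 93.0% at 5650 and 92.0% at 5424. On neither reading does moving from 5650 to 5424 decide whether 99% is right.

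**The case against.** The strongest reply is that nothing in the trial depends on 5650. Enrolment follows from attendance and means, not from a power target, and 6780 is correct. The power sentence keeps its printed value. The phrase used is a corrected sample size, not a count of patients analysed. The primary analysis is a mixed model on successive scores, the number of visits varies between patients, and methods for missing data are foreseen. Patients lost before three years can still contribute data, so neither 5650 nor 5424 is a hard analysis count.

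All of that stands, and it limits the point to a minor one. It does not reconcile the numbers: a stated loss of 20% and a stated remainder of 5650 from 6780 cannot both be right, and the power sentence uses the remainder.

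Three stronger readings are tempting and are not supported:

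- A reader might infer that the stated power is overstated. At the printed precision it is not, since 95.7% rounds to 96%.
- A reader might infer that the 99% figure fails because of this error. The check above shows no such dependence.
- A reader might point to rare categories, where power is much lower. The article gives no category split, and the shortfall there comes from imbalance rather than from the attrition figure.

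The cause is also not documented. Dividing by 1.2 instead of multiplying by 0.8 is probable, because it gives 5650 exactly. But 5650 is also 5 × 1130, five years of inclusions, and the article does not show the step.

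**Conclusion.** The corrected sample size is wrong as written. The article's own 20% loss leaves 5424 of 6780 patients, so the retained number is overstated by 226 (4.2% of 5424). This part is plain arithmetic on printed figures and needs no assumption beyond the usual meaning of a 20% loss.

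The effect on power is 96.4% against 95.7%. That comparison assumes equal groups and 0.1 as a standardised mean difference, tested two-sided at 0.05. Recruitment and design are unaffected. Severity is minor.

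**What to change.** In the Sample size section, replace 5650 with 5424 and restate the two-category power on that number: 95.7%, or 96% rounded, for equal groups, with the effect-size metric and the equal split named.

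Keep the expected loss at 20% unless there is a substantive reason to revise it. It is presented as an expectation for patients with cognitive disorders, and resetting it to 16.7% would only fit an assumption to a miscalculated number.

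The cost is one number and one restated power sentence. It needs no change to recruitment, design or analysis.

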#### Primary analysis

Univariate and multivariate analyses will be conducted to assess the relationship between the patient characteristics and the change in functional autonomy. Linear regression and ANOVA will be performed to assess the cross-sectional relationship between patient characteristics and functional autonomy scores. The successive assessments of the functional autonomy scores, considered as the dependent variables, will be modelled in a generalized linear mixed model to assess the longitudinal relationship between patient characteristics and change in functional autonomy [24–26]. The analyses will be adjusted for potential confounding factors when appropriate. An alpha level of 0.05 will be used for statistical significance, and tests will be bilateral.

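### The 99% power given for factors with more than two categories does not hold at the effect behind the 96%; it needs a larger effect that the text does not state

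*Protocol article*

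**What the plan says.** The Sample size section takes 6780 recruits (1130 per year for 6 years), allows for 20% loss to follow-up, and arrives at the number used for power: "the corrected sample size reaches 5650 patients". For a factor with two categories it claims an "effect size of 0.1 between the 2 patients categories, at a risk alpha of 0.05, with a power of 96"%. The next sentence extends this: "In case of factor with more than 2 categories, the power would reach 99"%. That sentence gives no effect size, no scale for it and no number of categories. The section then concludes that the number of patients appears adequate for the primary and secondary objectives. The Primary analysis section fixes the sidedness: "An alpha level of 0.05 will be used for statistical significance, and tests will be bilateral".

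**The concern.** Placed directly after the two-category figure and with nothing restated, the 99% reads as applying to the same number of patients, the same alpha and the same effect. On that reading power rises when categories are added. For an overall test with the size of effect (f) held fixed, the opposite happens: each extra category adds a numerator degree of freedom while the noncentrality stays the same, so power drops.

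This matters because several planned factors have, or are likely to have, more than two levels. Table 1 lists diagnosis and stage, educational level, socio-professional category and marital status. Diagnosis stage alone has at least three levels in the article's own terms: subjective cognitive decline, mild disorder and major disorder. A reader who takes the 99% at face value would give a null finding on such a factor more weight than the design supports at the effect just quoted.

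**Working it through.** **Inputs from the article.** N = 5650; alpha 0.05, two-sided; effect size 0.1, scale not named; stated power 96% (2 categories) and 99% (more than 2).

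**Assumptions.** Equal category sizes; one change value per patient; an overall one-way F test for k categories. The article does not give category sizes or k.

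**Step 1: reproduce the 96%.** With d = 0.1 and 5650/2 = 2825 per group:

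- d × √(N/4) = 0.1 × √1412.5 = 3.758
- power ≈ Φ(3.758 − 1.960) = Φ(1.798) = 96.4%

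The stated 96% is reproduced. For two equal groups f = d/2, so this effect is f = 0.05. Reading 0.1 as f instead gives more than 99.99% for two categories, so f = 0.1 cannot be what lies behind the 96%.

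**Step 2: hold that effect and add categories.** Power = P(F′ > F crit), where F′ is noncentral F with k − 1 and N − k degrees of freedom and noncentrality λ = N × f². At N = 5650 and f = 0.05, λ = 5650 × 0.0025 = 14.125 for every k.

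| Categories k | Power, N = 5650 | Power, N = 5424 |
|---|---|---|
| 2 | 96.4% | 95.7% |
| 3 | 93.0% | 92.0% |
| 4 | 89.9% | 88.5% |
| 5 | 86.9% | 85.4% |
| 6 | 84.2% | 82.4% |

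The last column uses 6780 × 0.8 = 5424, the number left after a 20% loss; the article's 5650 equals 6780/1.2. That is a separate point, and it does not alter this one. Using all 6780 patients does not rescue the 99% either: power at f = 0.05 is then 96.6% for k = 3 and lower for larger k.

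**Step 3: what effect would give 99%?** At N = 5650, 99% power needs f = 0.0616 (k = 3), 0.0645 (k = 4), 0.0669 (k = 5) or 0.0688 (k = 6). All exceed 0.05. Two natural readings of 0.1 go beyond these values:

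- **0.1 as Cohen's f:** λ = 5650 × 0.01 = 56.5, and power is above 99.99% for k = 3 to 6. This is twice the effect in Step 1 (d = 0.2 for two equal groups).
- **0.1 SD between each adjacent pair of ordered categories:** f = 0.1 × √((k² − 1)/12). For k = 3 this is 0.1 × √(8/12) = 0.082 and power is 99.99%; it is higher still for k = 4 and 5. The first-to-last gap is then 0.2 SD or more.

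**Step 4: a less favourable convention.** If 0.1 SD is the gap between the extreme categories and the means are evenly spaced, power is 79.0% (k = 3), 64.4% (k = 4) and 54.4% (k = 5). The article does not state this convention, so these figures only show how much the answer depends on what 0.1 means.

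**The case against.** The best defence is that the 99% is not an arithmetic error. The 0.1 is tied in the text to two categories, and the following sentence does not claim to reuse it. Cohen's f is a usual measure for ANOVA, which the Primary analysis section names, and at f = 0.1 the power does reach 99%. Steps of 0.1 SD between neighbouring categories also give it, and there power really does rise with more categories. What counts as the same effect across different numbers of categories is a matter of convention. The full protocol may state the scale. The article also describes the study as descriptive, and its size was set by attendance and resources.

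Much of this stands. A reader might infer that the 99% is simply miscalculated, or that it can arise only from reading 0.1 as f. The article supports neither, since it names no scale and at least two readings reach 99%. A reader might also infer that the cohort is seriously underpowered for multi-category factors. That does not follow: at f = 0.05 power is still 84% to 93% for 3 to 6 equal categories, and the much lower figures in Step 4 rest on a convention the article does not adopt.

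What does not stand is the presentation. Every reading that yields 99% uses a larger effect than the one behind the 96%, and the text does not say so. Condensation in a journal article may explain a missing detail, but here two stated figures are put side by side as if comparable.

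**Conclusion.** The point holds as a statement about comparability. At the effect that produces the 96% (d = 0.1, f = 0.05), with N = 5650, power for 3 to 6 equal categories is about 93%, 90%, 87% and 84%, which is 6 to 15 percentage points below the stated 99%. The direction of change is also the reverse of what the two sentences suggest. The 99% is attainable only at a larger effect that the article does not state; which one was intended cannot be determined from it. The figures rest on equal categories and an overall F test with f held constant.

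Severity is moderate. The figure supports the article's conclusion that the sample is adequate, and it becomes less favourable once put on one scale. No sample size, analysis or decision rule depends on it.

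**What to change.** Either of two changes resolves it:

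1. Replace the 99% sentence with power on the same scale as the 96%. For example: for the same effect (Cohen's f = 0.05, equal to d = 0.1 for two equal groups) and 5650 patients, power is 93%, 90% and 87% for factors with 3, 4 and 5 equal categories.
2. Keep the 99%, but state the effect size, its scale and the number of categories to which it applies, and say that this effect is larger than the one behind the 96%.

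If the retained number is separately corrected to 5424, the matching figures are 96% for 2 categories and 92%, 89% and 85% for 3, 4 and 5.

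The cost is one sentence and, under the first option, a less favourable stated power. No extra patients are needed and the planned analyses do not change.
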